#### Control condition

Both participants of the IG and the CG will have unrestricted access to treatment-as-usual (TAU). Participants of the CG will receive an online information letter with psycho-educative information about stress, depression and chronic pain. Additionally, a link to an online freely available audio CD with information about stress reduction is provided, as well as a link to a database with different health services and information about further treatment options in standard care (enhanced treatment as usual (TAU+) for the CG).

TAU will not follow a standardized protocol, however, health care consumption will be measured with the TiC-P [68] (see measures below). Hence, an accurate description of TAU can be provided.

### Sample size/power calculation

In this trial, the effectiveness of the IMI program in reducing depression severity is compared to TAU+. The estimation of sample size was based on a meta-analysis by Zhou and colleagues (2016) [26], who reported an effect size of *SMD* = 0.46 [95%-CI: 0.22–0.70] for IMIs in the reduction of subclinical depressive symptoms. In this meta-analysis mostly waitlist control groups where included. Since comparison of IG with TAU+ presumably yields a smaller effect size than comparison with waitlist control group [69], we assumed a conservative effect size of *d* = 0.35 for the present trial. An effect size of *g* = 0.35 [95%-CI: 0.23–0.47] was also reported in a meta-analysis as the effect of psychotherapy on reduction of depressive symptom severity in subthreshold depression with more than a half of the included studies applying care as usual in the CG [18]. Based on prior findings [23–25, 48–55], (Ebenfeld L, Lehr D, Ebert D, Kleine Stegemann S, Funk B, Riper H, et al.: Treating panic on the go: results of a randomized controlled trial evaluating a hybrid online-training for panic and agoraphobia symptoms, in preparation) and the above stated hypothesis, a one-sided t-test (α = 0.05; 1-β = 0.90) with a ratio of 1:1 (IG:CG) is used for power calculation. Power calculation was conducted with G*Power (Version 3.1.9.2) and resulted in an overall sample size of 282 participants. According to a meta-analysis approximately 28% percent of dropout occurred across a sample of studies evaluating efficacy and effectiveness of online-based interventions for depression with therapeutic support [69]. To compensate for an expected dropout of 28%, the present study aims at an overall sample size of 360 participants.

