### Objective and research question

The aim of the present study is to investigate whether a tailored IMI program targeting a variety of specific complaints associated with clinical depression is useful in reducing depressive symptoms and preventing onset of clinical depression as compared to enhanced treatment as usual (TAU+) within a 36-month follow-up period. We propose, that depressive symptomology will be reduced to a greater extent in the intervention group (e.g. IMI program) than in the control condition (e.g. TAU+) post-treatment (T1). The following research questions will be investigated in this pragmatic randomized controlled trial over a follow-up period of 36-months:
Is the IMI program effective in reducing depressive symptom severity compared to TAU+?Is the IMI program effective in preventing the onset of clinical depression as compared to TAU+?Is the IMI program effective in reducing various mental health outcomes (e.g. stress, anxiety, insomnia) compared to TAU+?Is there a differential or rather an undifferentiated, general effect of specific IMIs on different mental health outcomes?Is the IMI program superior in terms of cost-effectiveness and QALY health gains compared to TAU+?Which variables moderate and mediate the effects of the IMI program?What is the level of intervention satisfaction, adherence and acceptance to the IMI program?Are there negative effects of the IMI program?

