### Statistical analyses

#### Clinical analyses

All statistical analyses will be performed based on intention-to-treat (ITT) principle. Patterns of missing data will be examined and analyses will be corrected for missing data by applying multivariate imputation according to Van Buuren and Groothuis-Oudshoorn [117]. For those who substantially completed the intervention (at least 80% of the modules) additional per-protocol (PP) analyses will be conducted. Group difference between pre- and post-assessment nine weeks after randomization (T1) in primary outcome will be assessed using generalized linear modelling. Between-group effect size will be reported using standardized mean differences and 95% CIs at all measurement points. Reliable change index (RCI) and number needed to treat (NNT) will be calculated to determine clinical significance. Analysis of long-term effects will be adjusted to the data structure by using e.g. robust estimation of standard errors or mixed effect modelling. Group differences in depression onset will be assessed by calculation of a Poisson regression model. Incidence of clinical depression will be compared in IG and CG by calculation of incidence rate ratio (IRR). Other secondary outcomes like perceived stress, sleep quality, and quality of life will be analysed similarly as primary outcome. Additionally, moderation and mediation analyses will be performed.

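### The sample size rests on a one-sided 5% test, but the primary T1 difference is to be reported with a 95% CI, and the protocol does not link the two; power for that interval to exclude zero is about 83% at 282, not 90%

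*Protocol article*

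**What the plan says.** The section on sample size and power fixes the design error rates: "a one-sided t-test (α = 0.05; 1-β = 0.90". The effect size is set in the same place: "we assumed a conservative effect size of *d* = 0.35 for the present trial". Allocation is equal: "with a ratio of 1:1 (IG:CG) is used for power calculation". The calculation "resulted in an overall sample size of 282 participants", and the recruitment target follows from it: "To compensate for an expected dropout of 28%, the present study aims at an overall sample size of 360 participants". The reason given for testing in one direction is earlier trial findings "and the above stated hypothesis, a one-sided t-test", the hypothesis being the directional one in the objectives, that symptoms fall more under the IMI program than under TAU+ at T1.

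The section on clinical analyses assesses the T1 primary outcome by generalized linear modelling and gives neither α nor sidedness for that model. On reporting it says: "Between-group effect size will be reported using standardized mean differences and 95% CIs at all measurement points". Footnote a of Table 1 defines the primary outcome as the standardized mean difference between the arms at T1, so this interval belongs to the primary result as well as to the follow-up time points.

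**The concern.** A conventional 95% CI leaves 2.5% in each tail. A one-sided 5% test puts the whole 5% in the tail for benefit. The planned interval is therefore stricter than the rule that produced the sample size, and the 90% power does not carry over to it.

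Two things follow if the final test keeps the one-sided 5% level. A result with a one-sided p value between 0.025 and 0.05 would support the hypothesis while its published 95% CI includes zero, and the protocol does not say how to read it. In addition, the chance of wrongly claiming benefit would be 5%, twice the 2.5% implied by the interval printed beside the result. Expecting benefit from earlier trials explains the direction of the hypothesis; it is not in itself a reason for the looser threshold.

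**Working it through.** **Inputs, all from the sample size section:** d = 0.35; α = 0.05, one-sided; power 0.90; 1:1 allocation; 282 evaluable (141 per arm); 28% dropout; 360 recruited.

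**Method.** Two-sample t-test with n per arm, degrees of freedom 2n − 2, and noncentrality δ = d·√(n/2). One-sided power is P(T > t₀.₉₅). The 95% CI excludes zero when |T| > t₀.₉₇₅, so the power of that event is the two-sided 5% power. T is noncentral t with noncentrality δ.

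**1. Reproduce the stated figure.** For n = 141: δ = 0.35 × √70.5 = 2.939 and t₀.₉₅(280) = 1.650, giving power 90.1%. With n = 140 it is 89.9%, so 141 per arm is the smallest that reaches 90%. The stated 282 is reproduced exactly.

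**2. Change only the threshold, at 282.** t₀.₉₇₅(280) = 1.968 with the same δ gives power 83.4%. The difference due to sidedness alone is 90.1 − 83.4 = 6.7 points.

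**3. Apply the protocol's own dropout to 360.** 360 × 0.72 = 259.2 evaluable, about 129.6 per arm, δ = 2.817. One-sided power is 87.8%; two-sided power is 80.1%. The drop from step 2 arises because 360 is too few for 28% loss: 282/0.72 = 391.7, so 392 would be needed, whereas 282 × 1.28 = 361. From 360, 282 remain only if the loss is 1 − 282/360 = 21.7%.

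| Evaluable | One-sided 5% | 95% CI excludes zero |
|---|---|---|
| 282 | 90.1% | 83.4% |
| 259 | 87.8% | 80.1% |
| 360 (no information lost) | 95.2% | 91.2% |

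For reference, 90% power at two-sided 5% needs 346 evaluable (173 per arm).

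**4. Where test and interval disagree.** The smallest significant observed d is t·√(2/n). At 282, √(2/141) = 0.1191, so the limits are 1.650 × 0.1191 = 0.197 (one-sided) and 1.968 × 0.1191 = 0.234 (two-sided). An observed d between these is one-sided significant with a 95% CI that includes zero. If the true d is 0.35, the probability of landing there is the 6.7 points of step 2. At 259 the band is about 0.205 to 0.245.

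**5. Adjustment for T0 QIDS-SR16.** With a T0-T1 correlation r, the residual variance is multiplied by 1 − r², so the effective d is 0.35/√(1 − r²). The protocol gives no r; 0.3 and 0.5 are assumptions.

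| r | Effective d | Two-sided power, 259 | Two-sided power, 282 |
|---|---|---|---|
| 0.3 | 0.367 | 83.7% | 86.7% |
| 0.5 | 0.404 | 90.0% | 92.2% |

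**The case against.** The one-sided choice is disclosed, given a reason, and computed correctly. It is stated for the power calculation; the sidedness of the final model is a detail that an analysis plan may settle. The 95% CI is a way of reporting estimates at every time point, and nothing in the document makes it a test. The band of disagreement is narrow. The planned analysis also concerns change from T0 to T1, so baseline may enter the model and unadjusted power would then be the pessimistic end. All of this is fair. It rules out calling the passages a contradiction, and silence on sidedness in the analysis section is not itself the fault. What remains is that the only error rate the article states is one-sided 5%, that the interval planned for the same quantity conventionally implies 2.5%, and that nothing relates them.

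Three stronger readings are tempting and should not be made:

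- A reader might infer that the 95% CI is the trial's success criterion. No section says so.
- A reader might infer that one-sided testing by itself takes power from 90% to 80%. Sidedness alone takes it to 83.4%. The 80.1% also includes the dropout shortfall, which lowers the one-sided test to 87.8% as well.
- A reader might infer that a one-sided test undermines the research question "Are there negative effects of the IMI program" That question is addressed by the INEP and an open question, both recorded in the intervention group only. It does not depend on the sidedness of the T1 comparison, and worsening on the QIDS-SR16 would still show in the reported interval.

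One might also argue that imputation restores all 360, which would give 91.2%. Multiple imputation does not in general recover all the information lost to dropout, so that figure is an upper bound for the unadjusted analysis.

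**Conclusion.** The point holds as an unreconciled design α and reported interval. For d = 0.35, the power for the 95% CI to exclude zero is about 83% with the planned 282 evaluable and about 80% with 259, against the stated 90%. On available cases and without adjustment, 360 recruited with 28% dropout does not give 90% under either sidedness. These figures assume a two-sided 95% CI, an unadjusted comparison of available cases, and equal loss in both arms. Baseline adjustment could recover part or all of the shortfall, depending on a correlation that the protocol does not give. The matter deserves correction because it concerns how the primary result will be read, but it does not invalidate the design.

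**What to change.** Before the T1 result is known, add a statement that the primary test is two-sided at 5%, so that it agrees with the 95% CI already planned. Restate the power at that level for d = 0.35: about 83% with 282 evaluable or 80% with 259, unadjusted. If the model adjusts for T0 QIDS-SR16, which is already collected, say so and give about 84% to 90% at 259, marking the correlation of 0.3 to 0.5 as assumed. Fixing this in advance keeps the choice of threshold independent of the result.

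The cost is a sentence or two and a less favourable stated power. Recruitment has concluded, and no additional participants are asked for.

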#### Assessment of eligibility and randomization

People are screened for eligibility via an online screening questionnaire. Screening includes online questionnaires to assess the presence and the severity of depressive (PHQ-9 ≥ 5) and chronic pain symptomology (CPG ≥ Grade II + chronic pain longer than six months), as well as possible suicidal ideation. Online questionnaires include self-report of age, insurance status, and current psychotherapy. If the eligibility criteria are fulfilled, applicants will receive an online information letter including detailed information about study procedure and informed consent. They will be informed that they can withdraw from the intervention and/or study at any time without any negative consequences. After giving informed consent, participants will enter the study and complete baseline assessment (T0).

Subsequently, participants will be randomly allocated to intervention or control condition and will be informed about group membership via e-mail. Randomization will take place at an individual level. Randomization will be conducted by a person who is blind regarding all processes within the intervention. Whereas blinding of participants is not possible, data collectors are blinded regarding group membership. Group membership is only known by the persons administering allocated treatments to participants. The automated web-based programme sealed envelope (www.sealedenvelope.com) is used to perform permuted block randomization with randomly arranged block sizes (8, 10, 12) and an allocation ratio of 1:1.

Written informed consent for participation in online-assessments will also be obtained from e-coaches. No eligibility criteria are applied by the study team for selection and assignment of e-coaches. E-coaches are employed, assigned, guided and supervised by the GET.ON institute regarding their task of counselling the study participants.

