## Outcome measurements

### Primary outcome

#### Depressive symptom severity at post-treatment (T1)

The primary outcome is depressive symptom severity at post-treatment (T1), assessed with the German Version of the Quick Inventory Depressive Symptomology (QIDS-SR16) [75]. The 16-item self-report inventory covers all nine DSM-5 symptom criterion domains of MDD. The QIDS-SR16 is characterized by high internal consistency of α = .86 [75]. The items are rated on a 4-point-scale ranging between 0 and 3. The total score ranges between 0 and 27, with a higher score indicating higher depressive symptom severity. Whereas a score between 0 and 5 indicates normal health status, scores between 6 and 10 indicate mild depressive symptomology, between 11 and 15 moderate, between 16 and 20 severe and scores greater than 20 indicate very severe depressive symptomology. Since the QIDS-SR16 is sensitive to symptom change and provides very similar results compared to longer clinical ratings like HAM-D17, HAM-D21, and HAM-D24 [75], this inventory will be administered to monitor changes in depressive symptom severity.

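### The target of 360 does not cover the stated 28% dropout: it covers about 22%, and at 28% the planned test has about 88% power rather than 90%

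*Protocol article*

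**What the plan says.** The whole calculation is in the protocol article under Sample size/power calculation. The assumed effect is given as "we assumed a conservative effect size of *d* = 0.35 for the present trial". The test is specified as "a one-sided t-test (α = 0.05; 1-β = 0.90) with a ratio of 1:1 (IG:CG) is used for power calculation", which agrees with the randomisation section ("an allocation ratio of 1:1"). This calculation "resulted in an overall sample size of 282 participants". The dropout rate comes from published work on guided online interventions for depression: "According to a meta-analysis approximately 28% percent of dropout occurred across a sample of studies". The section then concludes: "To compensate for an expected dropout of 28%, the present study aims at an overall sample size of 360 participants".

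The Abstract repeats the total of 360. The article prints no inflation formula. It offers no other argument for 360, such as a gain from baseline adjustment. The primary endpoint is the QIDS-SR16 score at T1, nine weeks after randomisation. For missing values, the Clinical analyses section states that "analyses will be corrected for missing data by applying multivariate imputation".

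**The concern.** An allowance for dropout must leave the required number of participants after the losses. If a share q of those randomised is lost, the number to randomise is the evaluable number divided by (1 − q). Multiplying by (1 + q) is a common slip. It takes q as a share of the evaluable number, so it always falls short, and by more as q grows.

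The three figures printed here (282, 28% and 360) fit the second rule and not the first. The article therefore pairs a power with a dropout allowance that its sample size cannot deliver together. At stake is the accuracy of the power statement for the primary endpoint, which would normally be carried into the analysis plan and the results paper. The validity of the comparison is not at stake.

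**Working it through.** **Inputs**, all from Sample size/power calculation: d = 0.35; one-sided α = 0.05; power 0.90; 1:1 allocation; 282 evaluable; 28% dropout; 360 randomised.

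**1. Reproduce 282.** For a two-sample t-test with n₁ and n₂ per arm, the noncentrality parameter is d × √(n₁n₂ / (n₁ + n₂)) on n₁ + n₂ − 2 degrees of freedom.

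- 141 per arm: 0.35 × √70.5 = 2.94, power 0.9009.
- 140 per arm: power 0.8991.

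So 141 per arm, 282 in all, is the smallest balanced total that reaches 90%. The article's figure is right and has no slack. The two-sided version would need 346, so 282 is clearly the one-sided result.

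**2. Inflate for 28% dropout.**

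- Dividing by the share retained: 282 / (1 − 0.28) = 391.7, so 392 (196 per arm). Check: 392 × 0.72 = 282.2.
- Multiplying by 1.28: 282 × 1.28 = 360.96.

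The stated 360 matches the second line, after rounding down, and not the first.

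**3. What 360 leaves.** 360 × 0.72 = 259.2, so about 259 evaluable. The shortfall is 282 − 259 = 23, or 23 / 282 = 8%.

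**4. Dropout that 360 does cover.** 1 − 282 / 360 = 0.217, or 21.7%.

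**5. Power at 28% dropout.** With 129 + 130 participants, the noncentrality parameter is 0.35 × √(129 × 130 / 259) = 2.82 and power is 0.878. The gap to 0.90 is 2.2 percentage points. The effect detectable with 90% power at this size is d = 0.365.

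**6. Sensitivity to the dropout rate.** Number to randomise, 282 / (1 − q):

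| Dropout q | Number needed | Covered by 360? |
|---|---|---|
| 20% | 352.5 | yes |
| 22% | 361.5 | just short |
| 25% | 376.0 | no |
| 28% | 391.7 | no |

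**7. Could baseline adjustment make up the loss?** Adjusting for baseline QIDS-SR16 raises the effective standardised effect to d / √(1 − r²), where r is the correlation between baseline and T1. The article gives no value for r, so the following are assumptions, all with 259 evaluable:

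| Assumed r | Power |
|---|---|
| 0 | 0.878 |
| 0.2 | 0.889 |
| 0.3 | 0.903 |
| 0.4 | 0.922 |
| 0.5 | 0.945 |

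The break-even value solves 0.35 / √(1 − r²) = 0.3646, which gives r ≈ 0.28.

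**The case against.** The arithmetic cannot be disputed, but there is a fair case that it matters little.

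- **The loss is small.** A drop of 2.2 points in power, or a detectable effect of 0.365 instead of 0.35, is minor beside the uncertainty in the assumed effect. The two meta-analyses cited in the same section have 95% intervals of 0.22–0.70 and 0.23–0.47. This stands, and it limits the weight of the point.
- **The planned analysis is not an unadjusted t-test.** It is a generalized linear model of the pre-to-post group difference under intention to treat. If it adjusts for baseline, a correlation of about 0.28 is enough to restore 90%. That is possible, but the article states no correlation, does not say explicitly that the model adjusts for baseline, and bases its power on an unadjusted test. The trial's real power may reach 90%, but the printed justification for 360 still fails.
- **Imputation keeps all 360 in the analysis.** It does, but imputing a T1 score does not by itself restore the information lost when it was not observed. By inflating for dropout, the protocol accepts that dropout costs power.
- **The 28% may be intervention dropout.** The Discussion distinguishes leaving the intervention from leaving the study. People who stop the modules may still complete T1, particularly with payments and reminders. So 259 is conditional on 28% of T1 scores being missing in both arms together. That qualification stands. However, the protocol itself uses 28% as the loss to be compensated, and on that basis 360 is too few.
- **The multiplier is inferred.** This is true, since no formula is printed. The mismatch between 282, 28% and 360 holds however 360 was obtained.

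**Conclusion.** The concern holds. The claim that 360 compensates for 28% dropout is wrong on the article's own figures: 360 covers 21.7%, and 28% would require 392. At 28% dropout the stated test has 0.878 power for d = 0.35 instead of 0.90, with 259 evaluable participants, 23 short of the 282 required.

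This rests on reading 28% as the share of randomised participants without a T1 score, and on the unadjusted one-sided t-test that the article uses for its power. The error is clear but its effect is small. It does not affect the validity of the trial, and a baseline-adjusted primary analysis may offset it. It is a wrong statement to correct, not a design failure.

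**What to change.** Recruitment ended in April 2019, so the correction is to the statement and not to the target. Wherever the power is reported, in the analysis plan and the results paper, drop the claim that 360 compensates for 28% dropout and use wording such as:

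> With 28% dropout, 360 randomised participants yield about 259 with T1 data and about 88% power for d = 0.35 (one-sided α = 0.05, unadjusted t-test). Power of 90% requires dropout of at most 21.7%.

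If the primary model adjusts for baseline QIDS-SR16, the team may add that this can recover the shortfall. They should then state the assumed baseline–T1 correlation (about 0.28 or more is needed) and where it comes from.

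The cost is one corrected sentence and a slightly less favourable power figure. No participants are added, and no analysis or trial procedure changes.

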### Assessments

All assessments will be conducted online. For an overview of instruments at screening, baseline (T0), post-treatment (T1), and follow-up assessments (T2-T5), see Table 1. Participants will receive 10€ for completion of each follow-up assessment, starting with T1.

**Table 1 Tab1:** Overview of the assessments

Instruments	Aim	Time of measurement						
		Screening	T0	T1	T2	T3	T4	T5
Screening Instruments								
PHQ-9	Patient Health Questionnaire	✔						
CPG	Chronic Pain Grade Questionnaire	✔						
Chronicity of Pain	Pain longer for 6 months (yes/no)	✔						
Primary Outcome								
QIDS-SR16	Quick Inventory for Depressive Symptomatology		✔	✔^a^	✔	✔	✔	✔
Secondary Outcomes								
Adapted items from CIDI 3.0, CIDI-SC, and Epi-Q Screening Survey	Prevalence of major depression and bipolar disorder		✔	✔	✔	✔	✔	✔
PSS-10	Perceived Stress Scale		✔	✔	✔	✔	✔	✔
ISI	Insomnia Severity Index		✔	✔	✔	✔	✔	✔
GAD-7	Generalized Anxiety Disorder		✔	✔	✔	✔	✔	✔
PAS	Panic and Agoraphobia Scale		✔	✔	✔	✔	✔	✔
MPI	Multidimensional Pain Inventory		✔	✔	✔	✔	✔	✔
NRS	Pain Intensity (0–10)		✔	✔	✔	✔	✔	✔
AUDIT-10	Alcohol use disorder identification test		✔	✔	✔	✔	✔	✔
MBI-GS	Maslach-Burnout-Inventory (subscale emotional exhaustion)		✔	✔		✔		
AQoL-8D	Quality of life		✔	✔	✔	✔	✔	✔
SPE	Subjective prognosis of employment		✔	✔	✔	✔	✔	✔
Cost measurement								
TiC-P	Utilisation of health services, work-related productivity		✔	✔	✔	✔	✔	✔
Intervention-related Outcomes								
WAI-SR^b^, WAI-SRT^c^	Therapeutic relationship			✔		✔		
TAI-OT^b^	Technological alliance			✔	✔			
CSQ-I	Patient satisfaction			✔				
INEP^b^	Inventory of negative effects in psychotherapy			✔	✔	✔		
Negative effects^b^	Negative effects in psychotherapy			✔	✔	✔		
Other assessments								
Other questions	Socio-demographics		✔					
	Predictors for development of major depression		✔					
Diabetes	Diabetes diagnosis (yes/no)		✔					
BDI-II	Suicidality-Item	✔	✔	✔	✔	✔	✔	✔

^a^Primary outcome is the standardized mean difference between intervention and control group at T1. QIDS-SR16 will also be assessed at T0 and T2-T5

^b^Recorded in intervention group only

^c^Recorded in e-coaches only

*T0* Baseline, *T1* 9 weeks, *T2* 6 months, *T3* 12 months, *T4* 24 months, *T5* 36 months

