**Methods:**

A pragmatic randomized controlled trial (RCT) will be conducted to evaluate a tailored and therapeutically guided preventive IMI program in comparison to TAU+ with follow-ups at post-treatment (9 weeks), 6-, 12-, 24-, and 36-months. Entrepreneurs in green professions, collaborating spouses, family members and pensioners (*N* = 360) with sufficient insurance status and at least subthreshold depression (PHQ-9 ≥ 5) are eligible for inclusion. Primary outcome is depressive symptom severity (QIDS-SR16). Secondary outcomes include incidence of depression (QIDS-SR16), quality of life (AQoL-8D) and negative treatment effects (INEP). A health-economic evaluation will be conducted from a societal perspective. The IMI program is provided by psychologists of an external service company and consists of six guided IMIs (6–8 modules, duration: 6–8 weeks) targeting different symptoms (depressive mood, depressive mood with comorbid diabetes, perceived stress, insomnia, panic and agoraphobic symptoms or harmful alcohol use). Intervention choice depends on a screening of participants’ symptoms and individual preferences. The intervention phase is followed by a 12-months consolidating phase with monthly contact to the e-coach.

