#### Side effects of psychotherapy

Side effects of psychotherapy will be assessed with the Inventory for the Assessment of Negative Effects of Psychotherapy (INEP). The INEP records whether any negative changes, which are experienced during or after the treatment in the social and/or work environment, are attributed on the psychotherapeutic intervention [114]. In this trial, an adapted 22-item version covering possible negative effects associated specifically with online-trainings (e.g. concerns about data protection) is applied.

Additionally, an open question will be included for qualitative assessments of negative side effects of IMIs. Participants will describe experienced negative events and side effects, their time of beginning, their frequency, and their duration. Two further questions rate the negative impact of these events in the past and at present time.

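### The instruments for negative effects are given to the intervention group only and stop at 12 months; reliable deterioration on QIDS-SR16, measured in both arms to 36 months, is not named as the comparative measure

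*Protocol article*

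**What the plan says.** All references are to the protocol article.

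- **Objective and research question.** The eighth question is "Are there negative effects of the IMI program". The sentence that introduces the list places all questions in the randomised trial with its 36-month follow-up. Question 8 has no stated comparator, whereas question 1 reads "Is the IMI program effective in reducing depressive symptom severity compared to TAU" (TAU+).
- **Abstract, Methods.** "Secondary outcomes include incidence of depression (QIDS-SR16), quality of life (AQoL-8D) and negative treatment effects (INEP").
- **Assessments, Table 1.** INEP and the open question stand under "Intervention-related Outcomes", not under secondary outcomes. Both carry the footnote "Recorded in intervention group only" and are ticked at T1, T2 and T3 only. QIDS-SR16 is ticked at T0 to T5 with no arm restriction.
- **Side effects of psychotherapy.** INEP records whether negative changes "are attributed on the psychotherapeutic intervention", in a 22-item version adapted to online training. For the open question, "Participants will describe experienced negative events and side effects, their time of beginning, their frequency, and their duration".
- **Depression response and Clinical analyses.** The Jacobson and Truax method is applied to QIDS-SR16 under the heading of response. "Reliable change index (RCI) and number needed to treat (NNT) will be calculated to determine clinical significance". Clinical analyses also plans a Poisson model and incidence rate ratio for depression onset, and between-group effect sizes with 95% CIs at every measurement point.
- **Discussion.** The article lists as a strength that short- and long-term side effects are under-explored and that this trial will give detailed insight into positive and negative effects.

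**The concern.** A count of negative effects from the treated arm alone mixes three things: worsening caused by the programme, worsening that would have happened anyway, and measurement error. Self-attribution does not separate them reliably. Only the control arm can, and neither dedicated instrument is used there.

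The time horizon is also short. As described under Intervention, training takes 6 to 8 weeks and is followed by 12 months of monthly e-coach contact. For a participant who follows that course, the programme ends after T3, so neither instrument is given once it is over. Question 8 and the Discussion look further ahead than that.

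At stake is whether the trial can say anything comparative about worsening beyond what the onset threshold and group means reveal. The QIDS-SR16 data for this are collected in both arms to T5, but the article does not name the analysis.

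**Working it through.** The plan gives no rate of negative effects or deterioration, so there is no stated figure to reproduce. The check has three parts.

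**1. What the planned between-arm analyses capture.**
- *Onset (QIDS-SR16 of 13 or more).* A participant who moves from 6 to 12 worsens by 6 points and is not counted. A participant who is already at 13 or more at T0 cannot newly cross the line. The Discussion concedes that possible cases may be enrolled, because no upper severity limit applies. Conversely, a move from 12 to 13 counts, although one point may be measurement error.
- *Mean differences.* A favourable mean can coexist with a minority who worsen.
- *RCI.* It is planned, but as response and clinical significance; the worsening direction is not named.

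**2. Background deterioration without any harm.**
Input from Primary outcome: QIDS-SR16 internal consistency .86. Assumed, because the article gives neither: T0–T1 correlation r from 0.5 to 0.7, and mean change m from 0 to −0.4 baseline SD (negative means improvement). Changes are taken as normal with equal SDs at both times.

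RCI threshold = 1.96 × √(2 × (1 − 0.86)) = 1.96 × √0.28 = 1.037 SD.

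P(reliable deterioration) = 1 − Φ((1.037 − m) / √(2(1 − r))).

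| r | m | z | P |
|---|---|---|---|
| 0.5 | 0 | 1.037 / 1.000 = 1.04 | 15.0% |
| 0.5 | −0.4 | 1.437 / 1.000 = 1.44 | 7.5% |
| 0.7 | 0 | 1.037 / 0.775 = 1.34 | 9.0% |
| 0.7 | −0.4 | 1.437 / 0.775 = 1.86 | 3.2% |

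In an arm of 180 this is 0.032 × 180 ≈ 6 to 0.150 × 180 = 27 participants. The 6-to-12 example would count as reliable if the baseline SD is below 6 / 1.037 = 5.8 points.

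**3. Precision of a between-arm comparison.**
Arm sizes: 360 / 2 = 180 randomised; 180 × (1 − 0.28) ≈ 130 after the dropout assumed in the sample size section. Assumed rates: 8% and 4%.

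Half-width = 1.96 × √((0.08 × 0.92 + 0.04 × 0.96) / n) = 1.96 × √(0.112 / n).
- n = 180: 4.9 points.
- n = 130: 5.8 points.

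Both exceed the assumed 4-point difference, so that example interval would include zero. At 130 per arm, with assumed control rates of 5% and 10%, 80% power (two-sided 0.05) needs about 15.5% and 22.9% in the intervention arm.

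**The case against.** The strongest reply is that the design is not at fault. INEP asks about changes attributed to the training, and the control group receives no training to attribute anything to. Restricting it is a usual choice, Table 1 files it as intervention-related, and question 8 is not worded as a comparison. All of this stands. A reader might infer that the footnote contradicts the research question or is an error; the documents do not support that.

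A reader might also infer that the trial has no controlled evidence on harm. That is not supported either. The onset rate ratio compares a clinically important form of worsening between randomised arms: above 1 it would point to harm, below 1 to protection. Signed effect sizes at every time point add to this. What is missing is a measure of individual worsening that does not depend on the threshold of 13.

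It is tempting to propose the BDI-II suicidality item as a second ready-made endpoint, since Table 1 ticks it at T0 to T5. Procedure on suicidal ideations makes it conditional on a score of at least 1 on the PHQ-9 or QIDS-SR16 suicide item, so it is not a complete measure as it stands.

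Finally, tabulating RCI in the worsening direction could be left to an analysis plan that is not shown. That limits the weight of the point. It does not resolve the different labels for INEP in the abstract and Table 1, or the mismatch between a 36-month question and instruments that stop at 12 months.

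**Conclusion.** The point holds in a limited form. INEP and the open question give descriptive, self-attributed, intervention-group data to 12 months; they cannot show an excess over TAU+ or serve the 36-month horizon. Between-arm worsening is covered, but only indirectly, by the onset rate ratio and mean differences. A randomised comparison of reliable deterioration on QIDS-SR16 would give question 8 a direct comparator from data already planned.

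The 3% to 15% background rate shows why a comparator matters for worsening. It rests on the assumed correlation, mean change and normality, and it concerns QIDS-SR16 change, not INEP responses. The half-widths of 4.9 to 5.8 points rest on assumed rates of 8% and 4%. The comparison would therefore exclude only fairly large excesses; it would not settle whether small harms exist.

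**What to change.** 1. Keep INEP and the open question as descriptive data in the intervention group, and say so. Give INEP the same status in the abstract and in Table 1.
2. Limit statements based on these two instruments, in the 36-month framing of question 8 and in the Discussion, to T1 to T3.
3. Name a between-arm ITT comparison of reliable deterioration on QIDS-SR16 at T1 to T5, using the response RCI threshold with the opposite sign. Derive it from the imputed scores. Report risk differences with 95% CIs, read alongside the onset rate ratio.
4. If suicidality is compared, use the QIDS-SR16 suicide item, which belongs to the full scale given to both arms, or state how participants not routed to the BDI-II item are coded.

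**Cost.** Wording and analysis only; no new data. It adds five secondary estimates, or ten if suicidality is included at the same time points. All have limited precision and should be read as estimates with intervals, not as tests.
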